# Intestinal fatty acid binding protein as a marker for intra-abdominal pressure-related complications in patients admitted to the intensive care unit; study protocol for a prospective cohort study (I-Fabulous study)

**DOI:** 10.1186/s13049-015-0088-0

**Published:** 2015-01-16

**Keywords:** Abdominal Compartment Syndrome, Biomarker, Critical care medicine, Intensive Care Unit, Intestinal integrity, Intra-abdominal hypertension, Intra-abdominal pressure, Risk factors

## Abstract

**Background:**

Intra-abdominal hypertension (IAH) and abdominal compartment syndrome (ACS) have detrimental effects on all organ systems and are associated with increased morbidity and mortality in critically ill patients admitted to an intensive care unit. Intra-bladder measurement of the intra-abdominal pressure (IAP) is currently the gold standard. However, IAH is not always indicative of intestinal ischemia, which is an early and rapidly developing complication. Sensitive biomarkers for intestinal ischemia are needed to be able to intervene before damage becomes irreversible. Gut wall integrity loss, including epithelial cell disruption and tight junctions breakdown, is an early event in intestinal damage. Intestinal Fatty Acid Binding Protein (I-FABP) is excreted in urine and blood specifically from damaged intestinal epithelial cells. Claudin-3 is a specific protein which is excreted in urine following disruption of intercellular tight junctions. This study aims to investigate if I-FABP and Claudin-3 can be used as a diagnostic tool for identifying patients at risk for IAP-related complications.

**Methods/Design:**

In a multicenter, prospective cohort study 200 adult patients admitted to the intensive care unit with at least two risk factors for IAH as defined by the World Society of the Abdominal Compartment Syndrome (WSACS) will be included. Patients in whom an intra-bladder IAP measurement is contra-indicated or impossible and patients with inflammatory bowel diseases that may affect I-FABP levels will be excluded. The IAP will be measured using an intra-bladder technique. During the subsequent 72 hours, the IAP measurement will be repeated every six hours. At these time points, a urine and serum sample will be collected for measurement of I-FABP and Claudin-3 levels. Clinical outcome of patients during their stay at the intensive care unit will be monitored using the Sequential Organ Failure Assessment (SOFA) score.

**Discussion:**

Successful completion of this trial will provide evidence on the eventual role of the biomarkers I-FABP and Claudin-3 in predicting the risk of IAP-associated adverse outcome. This may aid early (surgical) intervention.

**Trial registration:**

The trial is registered at the Netherlands Trial Register (NTR4638).

**Electronic supplementary material:**

The online version of this article (doi:10.1186/s13049-015-0088-0) contains supplementary material, which is available to authorized users.

## Background

Patients undergoing major surgery or sustaining severe trauma are at risk of developing morbidity and mortality from postoperative or posttraumatic systemic inflammatory response syndrome, sepsis and multiple organ dysfunction. The development of such potentially lethal complications in otherwise healthy patients is poorly understood. Data from a prospective multicenter epidemiological study showed that intra-abdominal hypertension (IAH) is associated with increased morbidity and mortality rates in critically ill patients admitted to an intensive care unit (ICU) [1,2]. Therefore, early identification of patients at risk for IAH-related morbidity and mortality can be potentially lifesaving.

### Intra-abdominal pressure and intra-abdominal hypertension

Compliance of the abdominal wall together with the abdominal content determines the intra-abdominal pressure (IAP) level. Under physiologic situations, the IAP level is below 12 mmHg. Increased pressure in the abdomen is known as intra-abdominal hypertension (IAH). This is defined as a sustained IAP ≥12 mmHg [3]. IAH results in reduced blood flow to most organs, with consequent dysfunction of the cardiovascular, respiratory, renal, gastrointestinal, and central nervous systems. An IAP >20 mmHg in combination with new organ dysfunction is indicative of an abdominal compartment syndrome (ACS). The ultimate treatment of ACS is a decompressive laparotomy. Risk factors for ACS include leakage of an aneurysm of the abdominal aorta, closing the abdomen under pressure after abdominal surgery, damage control laparotomy, hyperhydration during hypovolemic shock, pancreatitis, and pulmonary contusion. These risk factors may apply to a majority of patients in the ICU. The mortality risk in patients with ACS may be as high as 80% [1].

The current gold standard measurement tool as put forward by the World Society of the Abdominal Compartment Syndrome (WSACS; http://www.wsacs.org/education/algorithms.html) is an intra-bladder pressure measurement. This is a simple, minimally invasive method, and the results are immediately available [3]. From a clinical perspective, however, the IAP level does not always represent the presence of intestinal ischemia and as such is not a perfect indicator for clinical outcome nor surgical therapy. Sensitive biomarkers indicative of early (*i.e.*, reversible) organ dysfunction are therefore needed as additional diagnostic tool. The combination of increased IAP and a biomarker level that represents organ damage would support the need for and timing of decompressive measures to relieve the abdominal pressure.

### Biomarkers released upon loss of small intestinal integrity

Evidence is accumulating that the intestines play a central role in the origin of postoperative and posttraumatic sequelae [4-6]. Enterocyte damage and tight junction loss can be triggered by IAH, and both result in loss of intestinal integrity. As a consequence, toxins, bacteria, and undigested food particles may pass the enterocyte layer, enter the underlying vasculature, and trigger systemic inflammatory reactions that may progress to multiple organ dysfunction syndrome and even death. Peptides released upon enterocyte damage (*e.g.*, Intestinal Fatty Acid Binding protein; I-FABP) or tight junction loss (*e.g.*, Claudin-3) are potentially ideal biomarkers that will help identify patients with early IAH-induced intestinal damage.

I-FABP is a small (14–15 kDa) protein that is exclusively present in mature enterocytes of the small and large intestine. It is released into the circulation upon enterocyte membrane integrity loss and rapidly excreted into the urine (half-life 11 minutes). Elevated I-FABP levels have been found in plasma, serum, and urine in patients with intestinal ischemia, celiac disease, systemic inflammatory response syndrome and necrotizing enterocolitis [7-15]. I-FABP levels can be measured sensitively in plasma, serum, and urine using an enzyme-linked immunosorbent assay (ELISA) [7,8].

Claudins are small (22 kDa) tight junction proteins [4,16-19]. Especially Claudin-3 is expressed in high quantities solely in the intestine [18]. The amount of Claudin-3 in the intestine decreases after tight junction integrity loss [17]. Breakdown of tight junctions by loss of Claudins (as measured on Western blots in urine) is an early event in intestinal damage, resulting in intestinal barrier loss [20].

The main aim of the current study is to investigate if urinary levels of I-FABP can be used as a diagnostic tool for identifying patients at risk for IAP-related complications. Secondary aims are to determine the same for serum levels of I-FABP and for urinary and serum levels of Claudin-3.

## Methods/Design

### Study design and setting

Multicenter prospective observational study of 200 patients admitted to the ICU of Erasmus MC, University Medical Center Rotterdam (Rotterdam, The Netherlands) or Radboud University Medical Center Nijmegen (Nijmegen, The Netherlands), who are at risk for developing IAH or ACS according to the definitions of the World Society of the Abdominal Compartment Syndrome [3]. Since it was suggested that patients who have undergone liver transplantation should also be screened for IAH [21,22], liver transplantation has been added to the list of risk factors. The study is registered at the Netherlands Trial Register (NTR4638).

### Study population and eligibility criteria

All adult patients admitted to the ICU who have at least two risk factors for developing IAH or ACS according to the WSACS will be eligible for inclusion [3].

Patients meeting the following inclusion criteria will be eligible for enrolment:Patients with at least two risk factors putting them at risk for IAH or ACS as agreed by the WSACS. Risk factors may be present already at admission, but also patients developing risk factors during ICU stay will be eligible from that moment onwards;Age 18 or older, with no upper age limit;Signed informed consent by patient or proxy.

If any of the following criteria applies, patients will be excluded:Patients in whom intra-bladder pressure measurement is contra-indicated. This includes patients with bladder trauma or hematuria;Patients in whom intra-bladder pressure measurements are not reliable due to intraperitoneal adhesions, bladder oppressive pelvic hematoma, abdominal packs in situ, (previous) bladder tumor or previous bladder removal;Patients with any inflammatory bowel disease that may affect I-FABP levels.

Exclusion of a patient because of enrolment in another ongoing drug or surgical intervention trial will be left to the discretion of the attending surgeon on a case-by-case basis.

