### Baseline, disease and treatment-related data

In addition to the outcome variables mentioned above, the following data will be collected:

***Intrinsic variables (baseline data)***:AgeGenderWeightHeightComorbidity

***Disease-related variables at admission***:Reason of admission to the ICU (*i.e.*, type of disease or injury and type of intervention)Serum lactate concentration at baseline (sodium fluoride tube)IAP level at baselineUrinary creatinine level at baseline (sediment tube)Acute Physiology and Chronic Health Evaluation II (APACHE II) score at baseline; this is a validated and commonly applied severity of disease classification system [24]. An integer score ranging from 0 to 71 is computed based upon 12 routine physiological measurements with a higher scores implying a more severe disease and a higher risk of death.Acute Physiology and Chronic Health Evaluation IV (APACHE IV) score at baseline; this standardized scoring metrics was developed in 2005 as an improved version of the APACHE II. The previously used set of equations were re-evaluated and improved where needed. The most important change involved the new categorization of disease groups [25].Simplified Acute Physiology Score II (SAPS II) at baseline; this score was designed to measure the severity of disease for patients admitted to Intensive care units aged 15 or more [26]. The SAPS II score is calculated from 12 routine physiological measurements during the first 24 hours of ICU admission, information about previous health status and some information obtained at admission. The computed score has a range from 0 to 163 points and a predicted mortality between 0% and 100%. Higher scores imply a more severe disease and a higher risk of death.Sequential Organ Failure Assessment (SOFA) score at baseline; this score is a validated and commonly used score to track a patient’s status during the stay in an ICU. The SOFA score is a scoring system to determine the extent of a person’s organ function or rate of failure [27-31]. The score is based upon six different scores, one each for the respiratory system (*i.e.*, PaO2/FiO2 ratio), the cardiovascular system (*i.e.*, mean arterial pressure and vasopressor requirement), the hepatic system (*i.e.*, bilirubin level), the coagulation system (*i.e.*, platelet count), the renal system (*i.e.*, creatinine level or urine output), and the neurological system (*i.e.*, Glasgow Coma Score). For each of these systems, a maximum of four points can be attributed. SOFA scores are determined on a daily basis during ICU admission.

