The prognostic role of the I-FABP and Claudin-3 on development of IAH, ACS, (increasing) organ dysfunction (based upon SOFA increase) or mortality will be assessed. This analysis will be performed with Stata software, version 10.0 or higher (StatCorp LP, College Station, TX, USA), using the generalized linear latent and mixed model (GLLAMM) framework. Herein, the binary outcome IAH (or new organ dysfuncion or ACS or mortality) will be used as dependent variable, and the level of I-FABP or Claudin-3 will be included in the model as time-dependent variable. Patient ID will be included as clustering variable as up to 13 measurements per patient will be available. Additional covariates such as age, gender, number of IAH risk factors, and BM will be entered into the model in order to evaluate their effect on the relation between biomarker level and outcome. Random intercept and slope will be considered. Results will be expressed as Odds Ratios with their corresponding 95% confidence interval and p-values.

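### The primary IAH–control comparison of I-FABP is unadjusted and the model names only the number of risk factors, so a difference may partly reflect the type of underlying insult rather than IAH

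*Protocol article*

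**What the plan says.** **Entry.** Study population and eligibility criteria admits "Patients with at least two risk factors putting them at risk for IAH or ACS as agreed by the WSACS". The risk factors that the Background names for ACS begin: "Risk factors for ACS include leakage of an aneurysm of the abdominal aorta, closing the abdomen under pressure after abdominal surgery, damage control laparotomy". It goes on to hyperhydration in hypovolaemic shock, pancreatitis and pulmonary contusion. Under Study design and setting, "liver transplantation has been added to the list of risk factors".

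**Influences on the marker.** The Background section on biomarkers reports raised I-FABP "in patients with intestinal ischemia, celiac disease, systemic inflammatory response syndrome and necrotizing enterocolitis". The opening of the Background says that major surgery and severe trauma carry a risk of SIRS. The one exclusion aimed at the marker is "Patients with any inflammatory bowel disease that may affect I-FABP levels"; the other clinical exclusions concern the bladder-pressure measurement.

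**Analysis.** Statistical analysis sets a univariate test of I-FABP between the IAH and control groups (t-test or Mann-Whitney). For the mixed model, with IAH, organ dysfunction, ACS or death as outcome and the biomarker as predictor, it says: "Additional covariates such as age, gender, number of IAH risk factors, and BM will be entered into the model". The same section acknowledges that risk factors differ between patients and permits, but does not require, subgroup analyses.

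**Data held.** The baseline list includes "Reason of admission to the ICU", covering the type of disease or injury and the type of intervention.

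**The concern.** The article's own text supplies both links of a possible confounding path. The type of insult is how patients qualify as being at risk of IAH. Some types are also tied, through ischaemia or SIRS, to raised I-FABP. If the mix of types differs between patients who develop IAH and those who do not, an unadjusted comparison picks up that mix.

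The count of risk factors does not address this. Two risk factors after abdominal vascular surgery and two in a patient with pulmonary contusion and heavy fluid loading have the same value. Optional subgroups do not give one adjusted estimate for the whole cohort.

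What is at stake is interpretation. The Background wants a marker of early gut damage caused by IAH, and foresees its use alongside IAP in timing decompression. If much of the I-FABP signal came from the admitting insult, the marker would add less to what is already known at admission, and the planned comparison could not show this.

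**Working it through.** **1. The plan's own figure.** Inputs from Sample size calculation: 120 controls, 80 IAH patients, two-sided α 0.05, 20.0 ± 10.0 v 30.0 ± 12.5 ng/mL, described as 0.5 SD.
- At 0.5 SD: z = 0.5 / √(1/120 + 1/80) = 0.5 / 0.1443 = 3.464; power = Φ(3.464 − 1.960) = 0.934.
- At the printed means and SDs: SE = √(100/120 + 156.25/80) = 1.669; 10 / 1.669 = 5.99; power above 0.9999.

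The stated power of more than 90% is reproduced either way. The point below does not touch the sample size.

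**2. What an ignored insult type could do.** The documents give no mix of risk factors, so these inputs are assumptions: IAH itself has no effect; a gut-related insult shifts I-FABP by g; it is present in a share p1 of IAH patients and p0 of controls; the SD within each type is 10 ng/mL (the plan's control SD).
- Spurious difference b = g × (p1 − p0).
- Variance per group = 100 + g² × p(1 − p).
- SE = √(var0/120 + var1/80).
- Rejection probability = Φ(b/SE − 1.96) + Φ(−b/SE − 1.96).

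Worked case, g = 15, 60% v 30%: b = 4.5; var0 = 100 + 225 × 0.21 = 147.25; var1 = 100 + 225 × 0.24 = 154; SE = √(1.227 + 1.925) = 1.775; b/SE = 2.535; rejection probability = 0.717.

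| g (ng/mL) | IAH v control | b (ng/mL) | Significant (nominal 5%) |
|---|---|---|---|
| 5 | 40% v 30% | 0.5 | 6.3% |
| 10 | 50% v 30% | 2.0 | 23.9% |
| 15 | 50% v 30% | 3.0 | 39.1% |
| 10 | 60% v 30% | 3.0 | 46.6% |
| 15 | 60% v 30% | 4.5 | 71.7% |

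The last row's bias is 45% of the planned 10 ng/mL. More extreme inputs go higher (g = 20, 70% v 30%: 98%), so the top of the range depends on the assumptions. If the insult were commoner among controls, b would change sign and could mask a real difference.

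**3. Does adjusting for the count help?** Least-squares simulation, 2,000 runs per case, no IAH effect, count of risk factors drawn independently of type. Cells give the share significant, with the mean estimate in ng/mL in brackets:

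| Case | Unadjusted | Count | Count and type |
|---|---|---|---|
| g = 10, 60% v 40% | 0.231 (1.95) | 0.229 (1.95) | 0.051 (−0.03) |
| g = 10, 60% v 30% | 0.474 (3.01) | 0.471 (3.01) | 0.050 (−0.01) |
| g = 10, 70% v 30% | 0.714 (4.00) | 0.710 (4.00) | 0.048 (0.00) |

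The count removes nothing when it is unrelated to type. If count and type were correlated it would remove part. Adding type restores the nominal level, provided that type is recorded correctly.

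**The case against.** **The size is assumed.** Prevalences, shift and direction are all chosen, and the mildest case is close to nominal. Controls also need two risk factors, so both groups are enriched. Excluding patients with abdominal packs or adhesions may remove some surgical cases. This stands: the calculation shows that the bias is possible and can be large, not that it is present. A reader might infer that the bias favours the biomarker; nothing in the documents settles that.

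**The risk factors are not shown to be gut insults.** A reader might infer that the entry criteria themselves release I-FABP. The article does not say so. It supports an indirect route, through ischaemia or SIRS, for some of them; it does not reproduce the full WSACS list, and pulmonary contusion is not described as a gut insult. The point therefore rests on a possible path.

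**The covariate list is open.** It is introduced by words that mark examples, this is a condensed article, and an analysis plan may name type. This stands for the model, so it would be wrong to say that the model adjusts only for the count. It does not reach the primary comparison, which the article states to be univariate.

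**The aim is diagnostic.** A predictor need not be free of confounding to predict. This stands and narrows the consequence to two matters: reading a difference as damage caused by IAH, and the value that I-FABP adds to admission type.

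**Conclusion.** The concern holds in this limited form. The primary comparison is fixed as unadjusted, the only risk-factor covariate named is the count, and the article acknowledges heterogeneity without requiring any analysis that deals with it. A group difference in I-FABP may partly reflect type of insult.

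Under the assumed imbalances tabulated above, false significance runs from about 6% to 72%. Those figures rest on no true IAH effect, a within-type SD of 10 ng/mL, and assumed shares and shifts.

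It does not follow that the biomarker cannot predict or that the sample size is wrong. Nor does it follow that the I-FABP exclusion must be widened to the other conditions listed in the Background. Enrolment began in April 2011, so a new exclusion such as coeliac disease would change eligibility in mid-study with no estimate of its benefit. Excluding ischaemic patients outright would remove the condition that the marker is meant to detect. The change is worth making before the analysis; the study can run without it, but its main result would then be hard to attribute to IAH.

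**What to change.** 1. Keep the unadjusted test. Beside it, pre-specify a regression of I-FABP on IAH status adjusted for admission or qualifying risk-factor type: for example abdominal or vascular surgery, trauma, pancreatitis, liver transplantation, other. Use the log scale if the values are skewed.
2. Derive the class from the reason for admission and type of intervention already collected. Fix it before IAH status is known; for patients already enrolled, code it by a written rule without sight of the pressure readings. Interventions made after IAH is recognised must not define it.
3. Add the same variable to the mixed model, beside the count.
4. Report as a sensitivity analysis the result without patients admitted for mesenteric ischaemia.
5. Leave the exclusion criteria unchanged. Do not use shock at T0 as an adjustment class: the article says that IAH impairs cardiovascular function, so shock may be its consequence.

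**Cost.** Some coding work and, with five classes, four degrees of freedom (residual 198 → 194). Precision falls slightly. In the two-class 60% v 30% case the overall share is (48 + 36)/200 = 0.42, and the squared correlation of type with IAH is 0.3² × 0.24 / (0.42 × 0.58) = 0.089. Variance then rises by 1/(1 − 0.089) = 1.10, and power at 0.5 SD goes from 0.934 to Φ(3.464/√1.097 − 1.96) = 0.91. For ACS, the cited general-ICU rate of 4% would give 200 × 0.04 = 8 cases, though more are expected in this at-risk cohort. With so few, the classes would have to be collapsed in that model.

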### Treatment

Patients with increased pressure determined by the intra-bladder pressure measurements will be treated in compliance with the algorithms for patient management as developed by the WSACS (www.wsacs.org/algorithms.php) [3]. The IAH Assessment Algorithm describes all risk factors that every patient should be screened for upon intensive care unit admission and upon clinical deterioration leading to new organ dysfunction. The intra-bladder pressure will be measured in patients with two or more risk factors for IAH or ACS or in patients who have undergone a liver transplantation. Patients who do not have two or more risk factors at baseline but develop new risk factors during their ICU admission will be followed from that moment onwards. The reason for this is that the occurrence of IAH during intensive care stay is known to be an independent predictor for mortality, whereas presence of IAH at intensive care admission is not [23]. Patients should be enrolled as soon as possible, but at least within 48 hours after meeting the eligibility criteria. The IAH/ACS Management Algorithm provides a decision tree for the follow-up of patients related to the IAP level. The IAH/ACS Medical Management Algorithm provides a stepwise approach of actions to be taken for achieving IAP pressure relief. In short, ICU management will be provided by the attending physicians and may consist of, among others, balanced intravenous fluid administration, correction of hypovolemia, electrolyte disturbances and/or anemia and analgesics.

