### Study procedures

In patient with ≥2 risk factors for IAH or ACS, the intra-abdominal pressure will be measured using an intra-bladder technique. The modified Kron technique described by Cheatham and Safcsak [33] will be applied for measuring IAP. In the current study, 20 mL of saline will be used in order to comply with the current recommendations of the WSACS. For the IAP measurement, a Foley catheter will be disconnected and a 3-way-valve will be inserted to create a continuous connection to a pressure transducer (DTXPlus™ PRESS PA, reference No 686496; Argon Critical Care Systems, Singapore). For every single measurement the valve connecting the urinary drainage bag is closed and 20 mL of saline is instilled. The midaxillary line will be used as reference.

During the first 72 hours after enrolment, IAP measurement will be repeated every six hours (Table 1). At those time points (including baseline), the following samples will be collected:

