**ASSESSMENTS:**			
**Baseline variables**	X		
**Disease-related variables**	X		
**IAP measurement**		X	
**Blood sample**		X	
**Urine sample**		X	
**I-FABP measurement**		X	
**Claudin-3 measurement**		X	
**Creatinine measurement**		X	
**Treatment-related variables**		X	
**SOFA score**		X	
**Adverse events**		X	X
**Length of ICU stay**		X	X
**Mortality during ICU stay**		X	X
**Secondary interventions**		X	X

*Patients are considered eligible as soon as two IAH risk factors are present. This can either be at ICU admission or later on during ICU stay.

**Patients are followed until 72 hours or until discharge from the ICU, whichever comes first. Measurements are performed every six hours.

Urine samples for measurement of I-FABP, Claudin-3 and creatinine levels: A single fresh specimen of urine will be collected from the urinary bladder catheter that is already in situ. Samples will be kept on ice and then frozen at −80°C in aliquots within two hours of collection.Blood samples for measurement of serum I-FABP levels (NB: this only applies to patients enrolled at Erasmus MC, Rotterdam, the Netherlands): A single blood sample (10 mL) will be drawn from the arterial line that is already *in situ*. Blood will be collected in pre-chilled vacutainer containing EDTA as anticoagulent (BD Vacutainer, Becton Dickinson Diagnostics, Aalst, Belgium) and kept on ice. Blood will be centrifuged at 4°C, 4000× g for 15 minutes. Serum will be stored in aliquots at −80°C within 2 hours until analysis.

The reason for following up on patients during the first 72 hours after enrollment is based upon our observation (unpublished data) that over 95% of patients that deteriorate clinically due to increased IAP will do so during the 12–24 hours. In order not to miss any patients that may deteriorate somewhat later (*e.g.*, due to leak at the surgical site), we have set the time frame at 72 hours.

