In order to assess if levels of I-FABP or Claudine-3 can be used as a prognostic marker for intestinal ischemia-related morbidity it is necessary to also collect clinical data of patients during their entire stay at the ICU. These data will be extracted from the ICU patient data management system (PDMS), where they are stored as part of clinical routine. This will be done using the APACHE II, APACHE IV, SAPS II and SOFA score, which will be collected routinely for any patient admitted to the ICU. Follow-up in the ICU will include a daily physical examination, vital signs monitoring, routine blood tests, and chest radiographs or other ancillary tests as required. The attending physicians will record complications and events as well as any (secondary) intervention performed such as decompression laparotomy.

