### Statistical analysis

Data will be analyzed at the end of the study using the Statistical Package for the Social Sciences (SPSS) version 21 or higher (SPSS, Chicago, Ill., USA) and will be reported following the STrengthening the Reporting of OBservational studies in Epidemiology (STROBE) guidelines. No interim analysis will be done. Normality of continuous data will be assessed by the Shapiro Wilk tests and by inspecting the frequency distributions (histograms). Homogeneity of variances will be tested using the Levene’s test.

Descriptive analysis will be performed in order to report baseline characteristics (intrinsic variables and disease-related variables) and outcome measures of the entire cohort as well as for the group of patients that develop IAH (IAH group; IAP of 12 mmHg or higher on two separate recordings) versus those that do not (control group). For continuous data mean and SD (parametric data) or medians and percentiles (non-parametric data) will be calculated and reported. For categorical data, numbers and frequencies will be calculated and reported for the entire cohort and for the IAH and the control group separately.

Univariate analysis will be performed in order to test the difference in the primary and secondary outcome measures between the IAH group and the control group. Continuous data such as the I-FABP level (primary outcome) of the Claudin-3 level (secondary outcome) will be tested using a Student’s *T*-test (parametric data) or a Mann Whitney *U*-test (non-parametric data). Chi-squared analysis will be used for statistical testing of categorical data such as the number of secondary interventions. A p-value <0.05 will be taken as threshold of statistical significance. Depending upon the number of patients within the cohort of the study that develop ACS and the mortality rate, similar tests will be used to compare data for those who developed ACS (or those who died) versus those who did not. The patient cohort to be included will be heterogeneous by nature, as IAH and ACS risk factors will differ between patients. If it is possible to identify subgroups of patients (*e.g.*, liver transplant patients) subgroup analyses may be performed. P-values <0.05 will be taken as threshold of statistical significance.

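### The prognostic models do not separate biomarker samples taken before decompressive laparotomy from those taken after it, although the marker is meant to support that decision

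*Protocol article*

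**What the plan says.** **Treatment.** Raised pressure is acted on during the study: "Patients with increased pressure determined by the intra-bladder pressure measurements will be treated in compliance with the algorithms for patient management". The medical management algorithm "provides a stepwise approach of actions to be taken for achieving IAP pressure relief". This section does not mention laparotomy. The Background does, as the ultimate treatment of ACS, and Study procedures has the attending physicians record "any (secondary) intervention performed such as decompression laparotomy".

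**Sampling.** Study procedures states: "During the first 72 hours after enrolment, IAP measurement will be repeated every six hours", with urine collected at each point including baseline, and blood at one of the two centres. The footnote to Table 1 gives the only end points: "Patients are followed until 72 hours or until discharge from the ICU, whichever comes first". Pressure relief does not end or split the series.

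**Grouping.** Statistical analysis defines the IAH group at patient level, by "IAP of 12 mmHg or higher on two separate recordings". Nothing ends that status once pressure has been relieved.

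**Analysis.** The IAH-control comparison tests the I-FABP level with a t-test or Mann-Whitney test and names no time point or summary. The prognostic models (GLLAMM framework) take IAH, ACS, new organ dysfunction or mortality as the binary outcome and the biomarker as a time-dependent variable, with up to 13 measurements per patient. The covariates given as examples are age, gender, number of risk factors and what is printed as BM. Type and number of interventions are collected, but no described analysis uses them to classify samples.

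**Purpose.** The Background and Discussion present the marker as support for the need for, and timing of, decompressive measures.

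**The concern.** A marker that is to help decide on decompression has to be judged on values available before that decision. Here the variable that triggers pressure-relieving treatment is also the one that defines IAH and is part of the definition of ACS. The treatment falls inside the sampling window, and the series runs on afterwards.

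In a decompressed patient, the later values describe the course after decompression. The models pool them with the earlier values as if both were equally informative about risk. This matters most for ACS, where the events are few and the decompressed patients are mainly the events themselves. The odds ratio for ACS could then rest largely on values that no clinician could have had when deciding. Organ dysfunction and mortality are affected in the same way, but less, because their events also include patients who were never decompressed.

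The stated kinetics add to this. I-FABP is described as "rapidly excreted into the urine (half-life 11 minutes", so protein released before decompression has left the circulation well before the next scheduled sample.

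**Working it through.** **1. The plan's own power figure.** Inputs from Sample size calculation: 120 controls, 80 IAH patients, means 20.0 and 30.0 ng/mL, SDs 10.0 and 12.5, two-sided α 0.05, power above 90%.
- SE = √(10²/120 + 12.5²/80) = √(0.833 + 1.953) = 1.67 ng/mL.
- On the stated means: 10/1.67 = 5.99, so power is above 99.9%.
- On the 0.5 SD wording: 0.5 × √(120 × 80/200) = 3.46, so power is Φ(3.46 − 1.96) = 93.4%.

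The stated figure is reproduced on either reading.

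**2. Scheduled samples per patient.** 72/6 + 1 = 13, which matches the article's maximum of 13.

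**3. Share of a decompressed patient's samples that come after decompression.** The article gives no time of decompression. It does say, from unpublished data, that over 95% of patients who deteriorate because of raised IAP do so in the 12–24 hour period. I assume that this clock starts at enrolment, that decompression follows promptly, and that the patient is sampled to 72 hours. The 48-hour row extends the range.

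| Decompression at | Samples after it | Share of 13 |
|---|---|---|
| 12 h | 10 (18 to 72 h) | 77% |
| 24 h | 8 (30 to 72 h) | 62% |
| 48 h | 4 (54 to 72 h) | 31% |

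**4. Share of all samples from ACS patients.** If a fraction q of ACS patients is decompressed, and all ACS patients are sampled equally, the share is q times the last column. At 24 h it is 62% for q = 1 and 31% for q = 0.5. The documents do not give q.

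**5. What the half-life implies.** 6 h = 360 min, and 360/11 = 32.7 half-lives. A sample taken six hours after decompression therefore reflects release at about that time. This says nothing about whether injured cells are still releasing the protein.

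**6. Effect on the IAH-control comparison.** The cited multicentre study, as reported in Sample size calculation, gives prevalences of 32% for IAH and 4% for ACS: 4/32 = 0.125, about one IAH patient in eight. I take an extreme case in which every ACS patient is decompressed and every I-FABP value from those patients returns to the control mean.
- Remaining difference = 10 × (1 − 0.125) = 8.75 ng/mL. 8.75/1.67 = 5.24, so power is still above 99.9%.
- On the 0.5 SD reading: 0.4375 × 6.93 = 3.03, so power is Φ(3.03 − 1.96), about 86%.

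On the stated means, decompression alone barely touches this comparison. On the weaker reading it costs a few points, and only in this extreme case.

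**The case against.** The strongest reply is that the article leaves the matter open. The IAH-control comparison names no sample, so a baseline or pre-treatment value is not excluded. The covariate list is given as examples, so a treatment term could be added. Interventions are recorded. All of this stands for the IAH-control comparison. It stands less for the prognostic models, because there the article itself fixes the repeated-measures structure, the full series and the time-dependent predictor.

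A second reply is that samples after treatment are legitimate data. In an observational cohort under guideline care, prognosis along the treated course is a fair question, and a parallel fall in IAP and biomarker is informative. That is right, and it is why the all-samples model should stay. It does not answer the narrower question of whether the marker can inform decompression.

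A third reply is that dropping late samples removes data selectively from the sickest patients. This also stands, and is the reason to show both results.

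A reader might go further and infer that treatment seriously dilutes the main IAH-control difference. The documents do not support this. The article does not say that later samples enter that comparison. A large loss of power would need treatment to normalise I-FABP in about half or more of the IAH samples, and no figure in the documents suggests that. Some of the listed care, such as fluids, electrolyte correction and analgesics, may also reach controls. Nor do the documents say how laparotomy itself affects I-FABP, so no direction can be argued from that.

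**Conclusion.** The concern holds for the prognostic models and is most serious for ACS. Up to 13 values per patient enter without distinction between those before and those after decompressive laparotomy. For a patient decompressed at 12 to 24 hours, 62% to 77% of scheduled samples would come after the decision the marker is meant to support. This rests on assumed timing, on sampling to 72 hours, and on decompressed patients being mainly ACS events; the share falls in proportion if fewer are decompressed.

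For the IAH-control comparison the effect is probably small: power stays above 99.9% on the stated means even in the extreme case, and is about 86% on the 0.5 SD reading. Its direction is uncertain, and the samples used are not stated.

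**What to change.** 1. In the prognostic models, above all the ACS model, use only samples taken before the first recorded decompressive laparotomy when judging whether the marker can inform decompression. Every patient stays in the analysis with the samples taken up to that point.
2. Report the all-samples model alongside, with a time-dependent indicator for samples taken after decompression.
3. Apply the same before-decompression restriction to the IAH-control comparison, and state which samples or summary it uses.
4. Take the clock time of each decompressive laparotomy from the patient data management system, so that every six-hourly sample can be classed as before or after.

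The cost is a few sentences of analysis text and one time field; clinical care and sampling do not change. There are two limits. Late samples are lost selectively from the sickest patients, so neither result should be shown without the other. Samples taken after medical pressure-lowering measures are not removed, so the restricted analysis is free of decompression but not of all treatment.
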